## Abstract

[^177^Lu]Lu-PSMA-617 radiopharmaceutical therapy has been approved for the treatment of patients with metastatic castration-resistant prostate cancer for up to 6 cycles. Unfortunately, this treatment is not curative and patients experience relapse, even after initially favorable responses. When this occurs, patients have limited treatment options. Readministration of [^177^Lu]Lu-PSMA-617 in patients who previously benefited from therapy and had limited toxicity seems to be a promising option, with retrospective studies reporting favorable outcomes. **Methods:** RE-LuPSMA is an investigator-initiated, single-arm, single-center, open-label, phase 2 clinical trial designed to study the efficacy and safety of rechallenge therapy using [^177^Lu]Lu-PSMA-617 in patients whose disease progressed after responding well to a previous regimen of [^177^Lu]Lu-PSMA-617. This study plans to enroll 40 patients with progressive metastatic castration-resistant prostate cancer who previously completed 4–6 cycles of [^177^Lu]Lu-PSMA-617 with a favorable response (i.e., ≥50% decrease in prostate-specific antigen [PSA] level at any point during the first [^177^Lu]Lu-PSMA-617 regimen). After the first regimen of [^177^Lu]Lu-PSMA-617, patients must meet VISION trial criteria on a prostate-specific membrane antigen (PSMA) PET/CT scan within 8 wk of the planned first cycle of rechallenge therapy. After enrollment, participants will receive up to 6 additional cycles of [^177^Lu]Lu-PSMA-617 (7.4 GBq every 6 wk). The primary endpoint is 12-mo overall survival (OS), measured from the start of rechallenge therapy. The study will have 80% power to detect a difference between the null hypothesis of 50% OS at 12 mo and the study hypothesis of 71% OS at 12 mo. Secondary endpoints include adverse-event rates, PSA response rates (proportion of patients with a decrease of 50% or greater in PSA level), biochemical progression-free survival (defined as the time until PSA level increases 25% and 2 ng/mL above the nadir), radiographic progression-free survival, and quality-of-life changes (measured using Functional Assessment of Cancer Therapy–Radionuclide Therapy and Brief Pain Inventory–Short Form). Enrollment began in August 2024, with a planned study duration of 45 mo.

The phase 3 VISION trial demonstrated that [^177^Lu]Lu-PSMA-617 radiopharmaceutical therapy (RPT) can improve overall survival (OS), radiographic progression-free survival (PFS), prostate-specific antigen (PSA) response, quality-of-life scores, and bone metastasis pain compared with standard of care alone in patients with progressing metastatic castration-resistant prostate cancer (mCRPC) who previously received 1 or 2 taxane-based chemotherapy regimens and at least 1 androgen receptor pathway inhibitor (ARPI) (1,2). The phase 3 TheraP trial found that, for patients with mCRPC for whom cabazitaxel was considered the next line of therapy, [^177^Lu]Lu-PSMA-617 RPT evoked a superior PSA response and fewer severe adverse effects compared with cabazitaxel (3).

In 2022, the Food and Drug Administration (FDA) and European Medicines Agency approved the use of [^177^Lu]Lu-PSMA-617 RPT for the treatment of patients with mCRPC who had disease progression after chemotherapy (4). The approved regimen consists of 6 cycles of treatment, approximately 6 wk apart, with one 7.4-GBq injection per cycle (5).

Unfortunately, this treatment is not curative, and patients experience relapse, even after initially favorable responses. When this occurs, patients have limited treatment options, given that they previously received taxane-based chemotherapy or ARPI regimens. Readministration of [^177^Lu]Lu-PSMA-617 seems to be a promising option for patients who responded well to treatment and experienced limited toxicity.

Rechallenge therapy, in which [^177^Lu]Lu-PSMA-617 is reintroduced to patients whose disease progresses after a treatment completion, has been reported in multiple small retrospective series (6–10). Overall, these studies have reported favorable PSA response rates, with 37%–73% of patients experiencing PSA declines of 50% or greater with rechallenge therapy (6–10). They also reported predominantly hematologic adverse events with minimal kidney toxicity. Furthermore, in the series reported by Violet et al., the 15 patients who received additional cycles of [^177^Lu]Lu-PSMA-617 RPT had significantly higher PSA response rates than did the 21 patients who were treated with a new line of systemic therapy (8).

Nevertheless, because of the retrospective nature and small sample sizes of these studies as well as the wide range of PSA response and adverse event rates, prospective data are needed to better inform treatment-making decisions for patients with mCRPC whose disease recurs after [^177^Lu]Lu-PSMA-617 RPT.

In this prospective phase 2 trial, titled RE-LuPSMA, we aim to evaluate the efficacy and safety of rechallenge therapy with [^177^Lu]Lu-PSMA-617 in patients with disease progression after responding well to a previous regimen of [^177^Lu]Lu-PSMA-617.

## MATERIALS AND METHODS

### Study Design

RE-LuPSMA is an investigator-initiated, open-label, single-arm, single-center, phase 2 trial conducted at the UCLA. This trial is financially supported by Novartis, is being conducted under Investigational New Drug application 169476, and was approved by the UCLA institutional review board (IRB23-001509). The trial is registered at ClinicalTrials.gov (NCT06288113).

The study was powered to determine the 12-mo OS rate of patients with mCRPC who previously had a favorable response to a first regimen of [^177^Lu]Lu-PSMA-617 and are treated with rechallenge therapy (for a maximum of 6 additional cycles). We hypothesized a 12-mo OS rate of 71%, compared with a null hypothesis of an OS rate of 50% with no rechallenge therapy. The planned sample size is 40 subjects to achieve 80% power. The planned study duration is 45 mo. The study design is presented in Figure 1, and the patient flowchart is provided in Figure 2. The full study protocol is provided in the supplemental materials, available at http://jnm.snmjournals.org.

**FIGURE 1. fig1:**
[figure not shown]
Study design.

**FIGURE 2. fig2:**
[figure not shown]
Patient flow chart. QOL = quality of life.

### Endpoints

The primary endpoint is the 12-mo OS rate, measured from cycle 1 day 1 of [^177^Lu]Lu-PSMA-617 rechallenge therapy, which will be estimated using the Kaplan–Meier method with a 95% CI. A 1-sample log-rank test (as used in the power calculation) will be applied to assess whether the observed OS rate exceeds the null rate of 50%, derived from the standard care arm of the phase 3 VISION trial (1).

The secondary endpoints are as follows:
Overall and grade 3 or greater adverse-event rates, assessed using Common Terminology Criteria for Adverse Events version 5.0 through study completion.PSA response rate (response defined as a decline of ≥50% on 2 PSA levels measured at least 3 wk apart) during [^177^Lu]Lu-PSMA-617 rechallenge therapy.Biochemical PFS (defined by Prostate Cancer Working Group 3 guidelines as an increase of 25% and 2 ng/mL above the nadir, confirmed by a second value ≥ 3 wk later (11)) through rechallenge study completion.OS rate measured from the start of the first regimen of [^177^Lu]Lu-PSMA-617 RPT (cycle 1 day 1) through rechallenge study completion.OS rate measured from the end of the first regimen of [^177^Lu]Lu-PSMA-617 RPT (day 1 of the final cycle) through rechallenge study completion.Radiographic PFS through study completion, defined as progressive disease on prostate-specific membrane antigen (PSMA) PET/CT (Table 1) (12) or SPECT/CT Table 2 (13), assessed using response assessment criteria.Proportion of patients who initially had bone pain of at least 4/10 in severity who achieved a pain response (i.e., improvement of at least 2 points from baseline without an overall increase in opiate use) through rechallenge therapy completion.Median change in the Functional Assessment of Cancer Therapy–Radionuclide Therapy score (14) through study completion.Median change in the Brief Pain Inventory–Short Form score through rechallenge therapy completion.Median change in performance status, measured using the Eastern Cooperative Oncology Group performance score, through rechallenge therapy completion.

**TABLE 1. tbl1:** PSMA PET/CT Response Assessment Criteria

Response	Definition
Complete response	Absence of any PSMA uptake and no new PSMA-negative tumors
Partial response	>30% decrease in PSMA-VOL with no new PSMA-positive or -negative tumors
Stable disease	<30% decrease in PSMA-VOL (with or without new PSMA-positive or -negative tumors), ≥30% decrease in PSMA-VOL with new PSMA-positive or -negative tumors, <20% increase in PSMA-VOL (with or without new PSMA-positive or -negative tumors), or ≥20% increase in PSMA-VOL without new PSMA-positive or -negative tumors
Progressive disease	>30% increase in PSMA-VOL (with or without sites of PSMA-positive or -negative tumors)

PSMA-VOL = total volume of all PSMA-positive tumors.

Adapted from (12).

**TABLE 2. tbl2:** SPECT/CT Response Assessment Criteria

Response	Definition
Complete response	Absence of any PSMA uptake and no new PSMA-negative tumors
Partial response	>30% decrease in PSMA-VOL with no new PSMA-positive or -negative tumors
Stable disease	≤30% change in PSMA-VOL and no new PSMA-positive or -negative tumors
Progressive disease	>30% increase in PSMA-VOL (with or without new PSMA-positive tumors) or PSMA-negative tumors.

PSMA-VOL = total volume of all PSMA-positive tumors.

Adapted from (13).

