### Eligibility Criteria

To qualify for enrollment, patients must meet all of the following inclusion criteria:
Age ≥ 18 y.Diagnosis of mCRPC.Prior regimen of chemotherapy for mCRPC allowed but not required.Previous treatment with at least 1 ARPI.Previous completion of 4–6 cycles of [^177^Lu]Lu-PSMA-617.Demonstration of favorable response to the first regimen of [^177^Lu]Lu-PSMA-617, defined as a decline of at least ≥ 50% in PSA level.Meets PSMA PET/CT VISION trial criteria (1): at least 1 lesion with PSMA uptake higher than that of the liver, no soft-tissue lesions larger than 1 cm with PSMA uptake less than or equal to the liver, PSMA PET/CT must be performed within 8 wk of the planned first cycle of rechallenge therapy and at least 6 wk after completion of the first regimen of [^177^Lu]Lu-PSMA-617.Eastern Cooperative Oncology Group performance score of 0–2.Sufficient bone marrow capacity (defined as white blood cells ≥ 2,500/μL, platelets ≥ 100,000/μL, hemoglobin ≥ 9.0 g/dL, and absolute neutrophil count ≥ 1,500/μL).Abilities to understand and sign an approved informed-consent form and comply with all protocol requirements.

Also, HIV-infected patients who have well-controlled HIV and a low risk of AIDS-related outcomes are eligible for inclusion.

Patients are not eligible for study inclusion if they have received myelosuppressive therapy or other RPT within the past 6 wk (including docetaxel, cabazitaxel, ^89^Sr, ^153^Sm, ^186^Re, ^188^Re, and ^223^Ra) or have an estimated glomerular filtration rate of less than 50 mL/min/1.73 m^2^.

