At the request of the FDA, our study protocol includes dosimetric analyses using a single-time-point SPECT/CT scan after each infusion of [^177^Lu]Lu-PSMA-617. The FDA raised the issue that, between the 2 regimens of [^177^Lu]Lu-PSMA-617 as well as any prior external beam radiotherapy, patients may exceed the maximum dose constraint for the kidneys. This constraint has been established as a BED of 39 Gy, using data from peptide receptor RPT (16). The protocol was modified to specify that if the calculated kidney BED exceeds 39 Gy, the total number of cycles must be adapted or limited to remain under the 39-Gy BED limit.

When the trial began, there was an additional inclusion criterion that patients must have had at least 1 course of prior chemotherapy, consistent with FDA indications for [^177^Lu]Lu-PSMA-617 RPT. This was removed in a protocol amendment after results from the PSMAfore trial showed that chemotherapy-naïve patients had a radiographic PFS benefit with [^177^Lu]Lu-PSMA-617 compared with a change in ARPI therapy (17), which led to FDA approval of [^177^Lu]Lu-PSMA-617 in chemotherapy-naïve patients as well.

Since this study began, we have considered several exploratory analyses. The first includes studying how the presence of concomitant medications affects OS and PSA response. This question has not been addressed by existing retrospective data. We plan to compare patients receiving any concomitant medication with patients receiving no concomitant medications using log-rank analysis. We also plan to compare patients receiving androgen-deprivation therapy or first-generation ARPIs with those who continued second-generation ARPIs using log-rank analyses. The second exploratory analysis includes evaluating whether the length of time between the initial [^177^Lu]Lu-PSMA-617 course and subsequent PSA progression affects OS and PSA response rates. We plan to compare patients with time intervals less than 12 mo versus time intervals greater than or equal to 12 mo using log-rank analysis.

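### The two secondary OS rates counted from the first regimen include survival time that eligibility guarantees, so they describe only patients who reached rechallenge; separately, log-rank is named for a yes/no PSA outcome

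*Protocol article*

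**What the plan says.** The Endpoints section sets three OS clocks.

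- **Primary:** "The primary endpoint is the 12-mo OS rate, measured from cycle 1 day 1 of" rechallenge therapy. Kaplan–Meier estimation, a 1-sample log-rank test and a VISION-derived null rate are attached to this endpoint.
- **Secondary, start origin:** "OS rate measured from the start of the first regimen of" [177Lu]Lu-PSMA-617, i.e. its cycle 1 day 1.
- **Secondary, end origin:** "OS rate measured from the end of the first regimen of" [177Lu]Lu-PSMA-617, defined as day 1 of the final cycle.

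Both secondary rates run through completion of the rechallenge study. The article gives them no time point, estimator, test or benchmark.

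The Eligibility Criteria require "Previous completion of 4–6 cycles of" [177Lu]Lu-PSMA-617, "Demonstration of favorable response to the first regimen of" that agent (a PSA decline of at least 50%), and a PSMA PET/CT done "at least 6 wk after completion of the first regimen of" it and before rechallenge. The introduction gives the cycle spacing: "The approved regimen consists of 6 cycles of treatment, approximately 6 wk apart".

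In the Discussion, the exploratory analyses ask whether concomitant medication, and the time from the initial course to PSA progression, affect OS and PSA response. For the interval the method is: "We plan to compare patients with time intervals less than 12 mo versus time intervals greater than or equal to 12 mo using log-rank" analysis. Log-rank is also the only method named for concomitant medication.

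**The concern.** A patient enters this trial only by surviving the first regimen, responding to it, progressing, and remaining fit enough for another course. Anyone who died earlier is never in the data. A survival clock that starts at the first regimen therefore counts enrolled patients as at risk over a period in which, by the entry rules, none of them could have died. This is guaranteed (immortal) time produced by left truncation.

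Without a label saying so, the two rates can be taken as survival from first treatment with [177Lu]Lu-PSMA-617. Set beside a series counted from first treatment, they would look better by construction, whether or not rechallenge does anything.

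A smaller, separate matter is that log-rank compares time-to-event curves. PSA response is defined under Endpoints as the proportion with a confirmed decline of at least 50%, which is a yes/no outcome.

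**Working it through.** The article states no figure for these two endpoints, so there is none to reproduce.

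**Step 1. Guaranteed time g.** With cycles about 6 weeks apart (introduction), day 1 of the final cycle falls at week 3 × 6 = 18 (4 cycles) or 5 × 6 = 30 (6 cycles). The screening PET adds at least 6 weeks (Eligibility Criteria) and precedes rechallenge. One month is 365.25/12/7 = 4.35 weeks.

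- End origin: 6 weeks = 1.4 months.
- Start origin, 4 cycles: 18 + 6 = 24 weeks = 5.5 months.
- Start origin, 6 cycles: 30 + 6 = 36 weeks = 8.3 months.

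These are minima. Time to progression lengthens g only where it runs past the 6-week gap, so it must not simply be added on top.

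**Step 2. Effect on the rate.** Assume exponential survival, as in the sample-size section, and take its 50% and 71% 12-month rates as illustrative hazards. If S is the true 12-month OS and death is impossible before g, the apparent 12-month OS is S^((12 − g)/12). The 12-month time point is my assumption.

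| Origin and gap | g (months) | True 50% reads as | True 71% reads as |
|---|---|---|---|
| End, minimum gap | 1.4 | 54% | 74% |
| Start, 4 cycles, minimum gap | 5.5 | 68.8% | 83.1% |
| Start, 6 cycles, minimum gap | 8.3 | 80.7% | 89.9% |
| End, 6-month gap (assumed) | 6 | 70.7% | 84.3% |
| Either origin, gap of 12 months or more | ≥ 12 | 100% | 100% |

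For example, 0.50^((12 − 5.52)/12) = 0.688. The last row may matter in practice: the Discussion plans a subgroup with at least 12 months from the initial course to PSA progression.

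**Step 3. Does delayed entry repair it?** Two simulations were run; all entry times and pre-progression hazards in them are assumptions.

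- *Entry unrelated to prognosis.* One constant hazard (50% at 12 months), entry uniform over 1.4–12 months (end origin) or 5.5–24 months (start origin). The naive Kaplan–Meier gave 72.4% and 91.5%. Kaplan–Meier with delayed entry at rechallenge gave 54.0% and 68.1%, against conditional targets of 54.2% and 68.7%. It recovers survival given that one is alive at the earliest entry time, which is still not the 50% from first treatment.
- *Entry triggered by progression.* Responders alive at 5.5 months, hazard 0.005–0.01 per month before progression, the article's 71% or 50% hazards afterwards, entry at progression, median time to progression 6 or 12 months. The ranges for OS from the first cycle 1 day 1 were:

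| Time | True, all such responders | Naive | Delayed entry |
|---|---|---|---|
| 12 months | 86–95% | 90–97% | 68–83% |
| 24 months | 52–78% | 55–82% | 34–59% |

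In every scenario delayed entry lay further from the truth than the naive curve. The reason is dependent truncation: patients enter the risk set just when their hazard rises.

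**Step 4. Exploratory comparisons.** The stated aim covers OS and PSA response rates, and the only named method is log-rank. That fits OS and does not fit a proportion.

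**The case against.** The strongest reply is that nothing is miscalculated. The article assigns Kaplan–Meier and the VISION benchmark to the primary endpoint only, and the estimator for the secondary rates may be set out in section 11 of the full protocol, which is not shown. As a description of total survival among patients who reached rechallenge, both rates are legitimate. This largely stands. It reduces the point to definition, labelling and use, but does not remove it, because the published definition carries no such condition.

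The size is also open to challenge. At its minimum gap the end origin gains only 3 to 4 points. The 69–81% figures assume a constant hazard from first treatment; in the progression-triggered scenarios the naive curve sat only modestly above the responders' true survival. This stands too: the figures show direction and possible scale, not the bias that will occur.

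A reader might go further in four ways that the documents do not support.

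- *That the primary endpoint is affected.* It is not; its clock starts at rechallenge cycle 1 day 1.
- *That the article sets these two rates against VISION.* It states no comparator for them.
- *That the comparison of intervals under and over 12 months suffers from immortal time.* The Discussion states no first-regimen clock. If PSA progression precedes rechallenge, the interval is a baseline variable, and on a rechallenge clock there is no guaranteed time.
- *That left-truncated Kaplan–Meier is the clean repair.* It needs entry time to be independent of survival, which is doubtful when progression triggers entry.

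**Conclusion.** The point holds as one of definition and interpretation for two secondary endpoints. That no enrolled patient can have died before rechallenge follows from the entry rules alone. The minimum of about 1.4 months (end origin) and 5.5–8.3 months (start origin) also assumes that first-regimen cycles were about 6 weeks apart. The conversion to at least about 54% and 69–81% for a true 50% further assumes exponential survival and a 12-month time point. The actual size cannot be stated, because the article gives neither the distribution of gaps nor the time point. The rates cannot be read as survival from first treatment, and good values would not be evidence that rechallenge works.

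The log-rank point is independent of this, confined to exploratory analyses, and rests on the article's own definition of PSA response.

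**What to change.** - Define both secondary rates as total survival from the first regimen, conditional on reaching rechallenge, and name the time point.
- Report the distribution of the interval from the first regimen (start and end) to rechallenge cycle 1 day 1 beside them.
- State that no efficacy conclusion will be drawn from them, and that they will not be compared with VISION or any other series counted from first treatment.
- Use delayed-entry Kaplan–Meier at most as a sensitivity analysis, stating that entry is triggered by progression and that independent truncation is therefore doubtful. It also leaves the selection of fit responders in place.
- For the exploratory comparisons, keep log-rank for OS, counted from rechallenge cycle 1 day 1, and compare PSA response with Fisher's exact test.

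The cost is a few lines of endpoint and analysis wording; the dates needed already define the endpoints. The downside is that the two secondary rates will support narrower claims.

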Renal toxicity	
Grade 2 with eGFR < 30 mL/min/1.73 m^2^	Withhold [^177^Lu]Lu-PSMA-617 until improvement or return to baseline.
≥40% increase in serum creatinine and >40% decrease in eGFR compared with baseline	Withhold [^177^Lu]Lu-PSMA-617 until improvement or return to baseline, then reduce dose by 20% to 5.9 GBq.
Grade ≥3	Permanently discontinue [^177^Lu]Lu-PSMA-617.
Dry mouth	
Grade 2	Withhold [^177^Lu]Lu-PSMA-617 until improvement or return to baseline; consider reducing dose by 20% to 5.9 GBq.
Grade 3	Withhold [^177^Lu]Lu-PSMA-617 until improvement or return to baseline, then reduce dose by 20% to 5.9 GBq.
Gastrointestinal toxicity	
Grade ≥3 that is not amenable to medical intervention	Withhold [^177^Lu]Lu-PSMA-617 until resolved to grade 2 or return to baseline, then reduce dose by 20% to 5.9 GBq.
Fatigue	
Grade ≥3	Withhold [^177^Lu]Lu-PSMA-617 until resolved to grade 2 or return to baseline.
Electrolyte or metabolic abnormalities	
Grade ≥2	Withhold [^177^Lu]Lu-PSMA-617 until improvement to grade 1 or return to baseline.
AST or ALT elevation >5 times ULN in absence of liver metastases	Permanently discontinue [^177^Lu]Lu-PSMA-617.
Other nonhematologic toxicity	
Any unacceptable toxicity	Permanently discontinue [^177^Lu]Lu-PSMA-617.
Any serious adverse event that requires treatment delay >4 wk	Permanently discontinue [^177^Lu]Lu-PSMA-617.
Any persistent and intolerable grade ≥2 adverse event	Permanently discontinue [^177^Lu]Lu-PSMA-617.

eGFR = estimated glomerular filtration rate; AST = aspartate transaminase; ALT = alanine transaminase; ULN = upper limit of normal.

During this trial, the only concomitant medications that patients are allowed to continue are androgen-deprivation therapy (e.g., leuprolide, relugolix), first-generation ARPIs (e.g., bicalutamide), local external beam radiotherapy, and concomitant prostate cancer therapies that were administered during the first regimen of [^177^Lu]Lu-PSMA-617 and continued afterward. Any other treatments for prostate cancer must be discontinued before the start of the trial. Second-generation ARPIs (e.g., abiraterone, enzalutamide, darolutamide, apalutamide) do not require a washout period. Chemotherapy agents (e.g., docetaxel, cabazitaxel) require a 6-wk washout period. RPTs (e.g., ^89^Sr, ^153^Sm, ^223^Ra) require a 6-wk washout period. Sipuleucel-T, olaparib, rucaparib, and pembrolizumab require a 4-wk washout period.

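### Pain response excludes opiate increases but not local radiotherapy, which patients may continue, so relief from irradiating a painful bone site can count as a rechallenge response

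*Protocol article*

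**What the plan says.** **Endpoint.** The Endpoints section lists as a secondary endpoint the "Proportion of patients who initially had bone pain of at least 4/10 in severity who achieved a pain response". It then spells out the response in a parenthesis: "improvement of at least 2 points from baseline without an overall increase in opiate use". Assessment runs to the end of rechallenge therapy. Opiate use is the only other pain treatment the definition takes into account.

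**Concomitant treatment.** The Investigational Plan gives a closed list: "the only concomitant medications that patients are allowed to continue are androgen-deprivation therapy", then first-generation androgen receptor pathway inhibitors, and then "local external beam radiotherapy, and concomitant prostate cancer therapies that were administered during the first regimen of" [177Lu]Lu-PSMA-617 and kept up afterwards. Other prostate cancer treatments must stop before the trial. Washouts are stated for chemotherapy and radiopharmaceutical therapies (6 weeks) and for four other agents (4 weeks). None is stated for external beam radiotherapy, and nothing restricts its site or purpose.

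**Planned analysis of concomitant treatment.** The Discussion describes an exploratory analysis: "The first includes studying how the presence of concomitant medications affects OS and PSA response". Pain response is not included.

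**Design.** "RE-LuPSMA is an investigator-initiated, open-label, single-arm, single-center, phase 2 trial conducted at the UCLA".

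**The concern.** The opiate clause accepts a principle: improvement that another pain treatment could have produced should not be credited to the study drug. Local radiotherapy is a second pain-relevant treatment that the article itself names as allowed, yet the definition does not deal with it. The opiate clause is unlikely to catch it either, because radiotherapy that works should lower the need for opiates.

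What is at stake is attribution. The pain-response rate will be read as an effect of rechallenge, and there is no concurrent group from which to judge how much of it came from radiotherapy. The expected direction of the error favours rechallenge.

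**Working it through.** The plan gives no expected rate, hypothesis or denominator for pain response, so there is no figure to reproduce. The check sets the sections side by side and then shows the scale on stated assumptions.

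**Step 1. Does an irradiated patient meet the definition?** Take a patient with baseline bone pain of at least 4/10 whose painful site is irradiated.

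| Condition in Endpoints | Met? |
|---|---|
| Baseline bone pain at least 4/10 | Yes, by construction |
| Improvement of at least 2 points from baseline | Yes, if radiotherapy relieves the pain |
| Opiate use not increased overall | Yes, if stable or lower |
| Any condition on radiotherapy | None stated |

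The patient is counted as a responder.

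**Step 2. Does this depend on how the permission is read?**
- *Narrow reading:* only radiotherapy already under way at entry may continue. With no washout stated, its relief can appear after baseline and within the assessment window.
- *Broad reading:* a course may also be started during the trial. Its relief then falls within the window, which covers up to six cycles about 6 weeks apart.

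The gap exists on both readings; the broad one gives it more room.

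**Step 3. Does another stated rule close it?**
- The exploratory analysis covers overall survival and PSA response only.
- Study Duration stops treatment for biochemical and radiographic progression, loss of benefit or investigator discretion, among other reasons. It does not name irradiation of a painful site, so such a patient may stay in the assessment window.
- There is no control arm.

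**Step 4. Scale.** Each response due to radiotherapy changes the rate by 1/n, where n is the number with baseline pain of at least 4/10. The documents do not give n; its ceiling is the planned 40.

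| n (assumed) | Change per patient |
|---|---|
| 10 | 1/10 = 10 points |
| 20 | 1/20 = 5 points |
| 40 (ceiling) | 1/40 = 2.5 points |

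A second illustration uses: observed rate = r + e(1 − r)q. Here r is the response rate without radiotherapy, e the share of these patients irradiated at a painful lesion, and q the chance that radiotherapy alone gives a 2-point improvement, with independence assumed. None of these values is in the documents.
- r = 30%, e = 20%, q = 60%: 0.20 × 0.70 × 0.60 = 0.084, so 38.4% is observed instead of 30%.
- Lowest over r 20–40%, e 5–30%, q 40–70%: 0.05 × 0.60 × 0.40 = 0.012, or 1.2 points.
- Highest over the same ranges: 0.30 × 0.80 × 0.70 = 0.168, or 16.8 points.

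This shows how the bias behaves; it does not estimate it.

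**The case against.** **The permission is unclear.** The list covers treatments patients may *continue*. A reader might infer that the plan openly allows new radiotherapy for pain that rechallenge has failed to control, and then scores that failure as a success. The text does not support this. Newly started radiotherapy is neither clearly permitted nor excluded, and irradiating one painful site is nowhere defined as treatment failure. This part of the objection stands. It does not remove the point, because a course already under way at entry creates the same problem.

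**The full protocol may deal with it.** The article refers to a supplementary protocol whose section 11 holds the analysis plan, and neither is shown. A handling rule may exist there. However, the article states the response definition in explicit terms and chooses which co-intervention to guard against, so the point concerns a stated rule and not a missing detail.

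**The size is unknown.** A reader might infer a shift of tens of percentage points. That would need several irradiated responders in a small subgroup, and the documents give neither number. This stands.

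**Other endpoints.** A reader might extend the point equally to the Brief Pain Inventory. That endpoint is a median change and is not restricted to patients with pain of at least 4/10, so a few irradiated patients would move it little. This stands too.

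**Impact.** This is one of ten secondary endpoints. No hypothesis, power or decision is attached to it.

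**Conclusion.** The point holds in a limited form. As printed, the definition can credit rechallenge with relief produced by radiotherapy to a painful bone site, and nothing else in the article corrects for this. The conclusion rests on two textual facts: opiate use is the only co-intervention condition, and local external beam radiotherapy is on the allowed list without a limit on site or intent and without a washout. It also assumes that at least some patients with baseline pain of at least 4/10 are irradiated at a painful site; the documents do not say how many.

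The expected direction is upward. The size cannot be derived beyond 1/n per patient. The primary 12-month overall survival analysis, the sample size of 40 and the safety stopping rule are untouched. It is worth correcting because the endpoint is reported as a benefit of treatment and the correction is small.

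**What to change.** 1. Reconcile the Endpoints section with the Investigational Plan, so that it is explicit whether the radiotherapy entry covers only courses already under way or also courses started during the trial. This asks for clarity only; no change to radiotherapy use is proposed.
2. Add to the pain-response definition: *and without external beam radiotherapy for bone pain between baseline and the response assessment*. Count patients irradiated for pain before a response as non-responders.
3. Report a sensitivity analysis using the definition as now printed, together with the number of patients whose classification differs.

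**Cost.** One sentence in the definition and one extra tabulation. The dates and indication of radiotherapy must be captured; the article does not say whether they are. The reported rate may be slightly lower. A patient irradiated at one site whose other bone pain improved with rechallenge would count as a non-responder. That is a real loss, and the sensitivity analysis makes it visible. The rule should be fixed before the data are analysed, since the trial is open-label and later case-by-case judgement would be hard to defend.
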